## Abstract

**Background:**

The progressive course of pulmonary fibrosis (PPF) is observed with variable prevalence in different entities of fibrosing interstitial lung disease (fILD). PPF is characterised by worsening respiratory symptoms, declining lung function and increasing extent of fibrosis on high-resolution computer tomography. In Germany, data are limited on the characteristics and management of such patients.

**Methods/Design:**

INSIGHTS-ILD is a prospective observational longitudinal registry designed to describe characteristics, management and course of newly diagnosed (incident) and prevalent patients with fILD on the long term. The registry uses a non-probability sampling approach to collect data on characteristics, therapeutic interventions, health-related quality of life and health economic parameters. It is planned to include 900 patients in ambulatory care in about 30 expert sites over three years. The study has been initiated in December 2021, and currently (January 2023) follows 360 patients.

**Discussion:**

The registry is expected to provide much-needed data on the characteristics, management, and trajectories of patients fILD in Germany. The start of the study comes at a time when new treatment options are available for PPF. We hypothesize that PPF represents a broad clinical phenotype that is differentially influenced by inflammatory and fibrotic pathomechanisms that need to be treated with anti-inflammatory and/or anti-fibrotic treatment strategies. This registry will allow comparisons with other countries. Gap analyses based on current guidelines for management of these patients will be possible.

*Trial registration* DRKS00027389 (registered on 7.12.2021), BfArM NIS 7562.

## Background

The term interstitial lung disease (ILD) describes a large, heterogeneous group of more than 200 disorders affecting the lung parenchyma with overlapping clinical, radiographic, and histopathologic manifestations [1]. ILDs have differing underlying aetiologies, treatment options, clinical presentations and courses [2]. The most common and most studied form of fibrosing ILD is idiopathic pulmonary fibrosis (IPF).

Overall, early and accurate (differential) diagnosis of ILD can be challenging, and it is difficult to predict disease progression and treatment response in an individual patient [3].

The progressive course of non-IPF pulmonary fibrosis has been termed PPF in the most recent international guideline [4]. PPF covers large sub-groups of patients with fibrotic lung diseases that clinically progress despite appropriate usual management and is now an everyday problem for patients and clinicians alike [5]. Pulmonary fibrosis is typically regarded as an indicator and predictor of disease progression, and the prognosis associated with an ILD is generally worsened by the development and/or progression of fibrosis [6].

Progressive fibrosis is characterized by worsening respiratory symptoms, deterioration in lung function, limited response to immunomodulatory therapies, decreased quality of life and, potentially, early death. However, aside from IPF, fibrosing ILDs may be clinically stable, especially if the disease is mild. To date, several criteria for “progressive fibrosis” have been defined. It has been suggested that patients meeting any of the following criteria within a 24-month period have experienced disease progression: a relative decline of ⩾ 10% in forced vital capacity (FVC); a relative decline of ⩾ 15% in diffusing capacity of the lung for carbon monoxide (DLCO); or worsening symptoms or a worsening radiological appearance accompanied by a ⩾5– < 10% relative decrease in FVC [3, 6, 7]. In the most recent ATS/ERS/JRS/ALAT practice Guideline the guideline committee, suggested the presence of two out of three categories: 1. worsening respiratory symptoms, 2. worsening lung function or 3. increase of fibrosis on HRCT morphology within one year to make a diagnosis of PPF. It is commonly accepted that these criteria are only valid if other reasons for worsening have been excluded [4].

Improved survival from this disease spectrum may be dependent on better understanding of the epidemiology of the disease, its diagnostic spectrum and an analysis of outcomes from emerging therapies at a significant level [8]. Therefore, it is important to obtain detailed data on the natural course of fibrosing ILDs and their PPF phenotype, to understand patient characteristics, the situation and management of these patients in clinical practice.

Among the PPF, in Germany the collection of real-world data has focused on IPF (e.g. eurIPFnet [9], INSIGHTS-IPF [10–12]), and to a lesser extent on the other ILDs (GOLDnet [13], EXCITING [14]).

The newly initiated registry INSIGHTS-ILD can document fibrosing ILDs and their PPF in the context of the introduction of new therapies and complement the data from randomised controlled trials. It may serve quality assurance purposes, as individual centres can compare their results with other centres and with what is stated in guidelines.

## Rationale and aim

The present INSIGHTS-ILD disease registry aims to provide comprehensive information on different aspects of PPF within routine clinical practice: patient characteristics, diagnosis, management (including utilization, effectiveness and safety of medication), clinical course, quality of life and other patient related outcomes (PRO), and economic variables.

It documents all PPF with the exception of IPF since the latter entity has been documented in great detail in another registry named INSIGHTS-IPF [10–12].

## Objectives and endpoints

The objectives and corresponding endpoints of the registry are shown in Table 1.

**Table 1 Tab1:** Objectives and endpoints

	Objectives	Endpoints
Primary	To compare various PPF groups and treatment strategies in terms of characteristics and outcomes (lung function, survival, quality of life, other)	Time to progression of disease (any one of the following): Decrease of FVC > 10% predicted within one year Decrease Dlco > 15% predicted plus initiation of LTOT or permanent increase of oxygen flow when LTOT is established within one year Decrease of 6-MWD > 50 m within one year Hospitalization due to respiratory decompensation Death of any cause Change of treatment strategy (stop of anti-inflammatory or antifibrotic therapy, initiation of new anti-inflammatory or antifibrotic therapy or a combination of both)
Secondary	To assess drug utilization	Treatment strategy (immunosuppression, antifibrotic therapy) Dose and dosing schedule Duration of treatment (persistence) Switches between treatments Phases without drug treatment (with reasons) Reasons for drug discontinuation
	1. To determine risk factors for progression of disease 2. To determine factors for treatment success or failure, respectively, defined as clinical, functional, and radiographic stabilization (i.e. absence of deterioration in each of the categories) and change of treatment strategy (i.e. stop/start of antifibrotic therapy; stop/start of immunosuppressive therapy)	Survival Clinical symptoms Dyspnea Cough Lung function Annual DLCO decline Annual FVC decline 6-min walk distance QoL scores over time Radiographic course: fibrosis on HRCT Therapy escalation Clinical events (exacerbations, hospitalisations) Analyses stratified according to different diagnosis groups
	3. To determine potential biomarkers, which are routinely measured in many centers, to differentiate inflammatory driven from fibrosis driven progress	Laboratory parameters: CRP LDH Differential blood cell count (lymphocytes, neutrophils, eosinophils, monocytes), BAL differential cell count (as available)
	To assess safety	Adverse Events Adverse Drug Reactions

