## Observational plan

### Design

This ILD registry allows for structured, non-interventional collection of data. Participating physicians will not be subject to any instructions with regard to the diagnosis and therapy of their patients. All examinations performed depend on the discretion and clinical routine of the physician.

The registry contains a basic set of variables (mandatory data) which are essential for all included patients. Another set of variables (facultative data) can be requested from the participating sites but is left to their discretion. The platform is capable for substudies (i.e., addition of further variables) in selected centres to facilitate research collaboration between institutions.

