Comparison of patients treated with and without antifibrotic therapy in terms of mortality, pulmonary function test results and other outcomes will be performed on group level and not on single drug level (nintedanib, pirfenidone) as described in the following. The entire observation period will be considered for each patient in the registry in order to compare outcomes of interest. The observation time will start for each patient at registry enrolment in order to avoid immortal time bias (= “waiting time bias” bias due to exposure misclassification). Patients may start and stop new treatments such as antifibrotic therapy during follow-up. All available treatment episodes reported in the registry will be used in order to analyze the association between treatments and outcomes. At least two treatment periods will be assigned to patients who started antifibrotic therapy during follow-up; namely, a treatment period without antifibrotic therapy after enrolment, and another with antifibrotic therapy after treatment initiation. The episode before the start of antifibrotic therapy will be included in the mortality and other outcome analyses of the “no antifibrotics” group to account for immortal time bias. The analyses will be performed by generalized mixed models including time-dependent covariates. All analyses are planned on the group level (antifibrotic therapy yes / no), the exposition time to any antifibrotic therapy is used for analyses. Information on the specific drug is descriptively provided (percentage of patients on the drugs at BL, 6, 12, 18, 24 and 30 months). Detailed information (on product, dose and treatment dates) on previous (and current) therapy for pulmonary fibrosis will be collected.

Comparison of the two treatment groups in terms of lung function data and 6MWD test results will be analyzed by propensity score weighted linear mixed models to account for the possibility of more than one treatment episode for a single patient (additional cluster variable), and to account for the longitudinal study design, which was based on observed values. Intention to treat analyses will be additionally performed if it will be appropriate.

Further statistical methods planned include propensity score technique, multiple imputations, competing risks analyses, and latent class analysis to determine cluster of patients.

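### For treatment comparisons, the primary composite overlaps with the exposure: starting or stopping a therapy counts as progression, so the comparison is confounded with prescribing by construction.

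*Protocol article*

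**What the plan says.** In the protocol article, Table 1 (Objectives and endpoints), the primary objective is "To compare various PPF groups and treatment strategies in terms of characteristics and outcomes (lung function, survival, quality of life, other"). The endpoint in the same row is "Time to progression of disease (any one of the following"), followed by six components. Five are functional or clinical: a fall in FVC, a fall in DLCO together with new or increased long-term oxygen, a fall in 6-minute walk distance, and "Hospitalization due to respiratory decompensation Death of any cause". The sixth is "Change of treatment strategy (stop of anti-inflammatory or antifibrotic therapy, initiation of new anti-inflammatory or antifibrotic therapy or a combination of both"). It carries no condition on why therapy was changed.

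Other sections bear on how often the sixth component can occur:

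- Patients: everyone eligible is already on anti-inflammatory, immunomodulatory or antifibrotic therapy at entry.
- Design: "Participating physicians will not be subject to any instructions with regard to the diagnosis and therapy of their patients".
- Descriptive analysis and statistical testing: "Patients may start and stop new treatments such as antifibrotic therapy during follow-up". Antifibrotic use is treated as a time-dependent exposure: "At least two treatment periods will be assigned to patients who started antifibrotic therapy during follow-up", one before the start and one after it.

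**The concern.** Treatment strategy is the compared factor in the primary objective, and a change of treatment strategy is an event in the primary endpoint. A stop for intolerance, at the patient's wish or after sustained improvement counts the same as a fall in FVC or a death, and all are labelled progression. The Background describes progression by symptoms, lung function and imaging; none of the criteria set out there includes a treatment change.

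At stake is the reading of the primary endpoint by treatment strategy. Part of any difference would reflect how often physicians change therapy in each group. There is also a possible clash with the plan's handling of immortal time. If time to first event were analysed in the off and on periods, starting an antifibrotic would close the off period with an event, and the on period would have nobody left at risk of a first event.

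**Working it through.** **The plan's own figures.** The article states no event rate, switch rate, effect size or power for the primary endpoint, so there is no figure to reproduce on this point. Its only calculation is the rule of three under Sample size: 3/900 = 1/300 and 3/(900 × 2.5) = 1/750. Both reproduce, and neither bears on this question.

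**Step 1: effect on the hazard ratio.** Assume constant, independent hazards. Let d be the yearly rate of the five disease components under strategy B, HR_d the true disease hazard ratio (A v B), and s_A and s_B the total yearly rates of any treatment change in each group. These totals cover starts and stops of both drug classes, because patients in either group can have either kind. Then

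composite HR = (HR_d × d + s_A) / (d + s_B).

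All rates below are assumptions.

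| d | s_A v s_B | HR_d = 1.00 | HR_d = 0.70 |
|---|---|---|---|
| 0.2 | 0.1 v 0.1 | 0.30/0.30 = 1.00 | 0.24/0.30 = 0.80 |
| 0.2 | 0.3 v 0.1 | 0.50/0.30 = 1.67 | 0.44/0.30 = 1.47 |
| 0.2 | 0.1 v 0.3 | 0.30/0.50 = 0.60 | 0.24/0.50 = 0.48 |
| 0.3 | 0.1 v 0.1 | 0.40/0.40 = 1.00 | 0.31/0.40 = 0.775 |
| 0.3 | 0.3 v 0.1 | 0.60/0.40 = 1.50 | 0.51/0.40 = 1.275 |
| 0.3 | 0.1 v 0.3 | 0.40/0.60 = 0.67 | 0.31/0.60 = 0.52 |
| 0.5 | 0.1 v 0.1 | 0.60/0.60 = 1.00 | 0.45/0.60 = 0.75 |
| 0.5 | 0.3 v 0.1 | 0.80/0.60 = 1.33 | 0.65/0.60 = 1.08 |
| 0.5 | 0.1 v 0.3 | 0.60/0.80 = 0.75 | 0.45/0.80 = 0.56 |

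A smaller imbalance of 0.2 v 0.1 is enough to hide a true 0.70: 0.34/0.30 = 1.13, 0.41/0.40 = 1.025 and 0.55/0.60 = 0.92 for d = 0.2, 0.3 and 0.5. With s_A = s_B = 0 the formula returns HR_d, so leaving the component out removes the distortion.

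**Step 2: time at risk after an antifibrotic start.** Take patients without an antifibrotic at enrolment, start rate s, no drug effect and T = 2.5 years (the observation time that the article uses conditionally).

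- With the component, each patient's time at risk ends at the earliest of disease event, start or T. On-treatment time at risk is 0.
- Without it, mean time at risk is (1 − e^(−dT))/d, of which (1 − e^(−(d+s)T))/(d+s) is off treatment.
 - d = 0.5, s = 0.1: 1.427 years, of which 1.295 off; on-treatment share 0.132/1.427 = 9%.
 - d = 0.2, s = 0.3: 1.967 years, of which 1.427 off; on-treatment share 0.540/1.967 = 27%.

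A simulation over d = 0.2 to 0.5 and s = 0.1 to 0.3 gave the same 9% to 27%, with an on/off rate ratio of 1.00 to 1.01, as it should be with no effect.

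**The case against.** The strongest reply is that the problem reaches less far than it first appears, and several parts of that reply stand.

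- **Disease still drives much of the endpoint.** A reader might infer that the result is set by prescribing and not by disease. The documents do not support that. Five of the six components do not depend on a drug change, and with equal change rates a null stays null.
- **The episode split is not expressly applied to the composite.** For the antifibrotic yes/no comparison, the statistical section names mortality, lung function and unspecified other outcomes. A reader might infer that starters always lose their on-treatment time. That holds only if the composite is analysed as time to first event within the off and on periods, which Table 1 permits but the statistical section does not state. For mortality, FVC, DLCO and 6-minute walk distance, on-treatment time counts in full.
- **The size is unknown.** A model in which antifibrotic patients can only stop and the others can only start would misstate the endpoint, since anti-inflammatory changes count in both groups. The figures above use total change rates but remain illustrations.
- **The aims are mainly descriptive.** No confirmatory test of the composite is stated, and the components are recorded separately, so a narrower composite can be derived later.

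These points limit the claim without removing it. Table 1 assigns this composite to the comparison of treatment strategies, and a descriptive curve of time to progression that counts tolerability stops is still mislabelled. Details left to the SAP would not alter the definition as printed.

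**Conclusion.** The point holds for the comparison of treatment strategies on the primary endpoint. Exposure and outcome overlap by definition, and nothing else in the article repairs this. Under the assumed disease-event rates of 0.2 to 0.5 per year, change rates of 0.3 v 0.1 move a null hazard ratio to 1.33 to 1.67 and turn a true 0.70 into 1.08 to 1.47. The opposite imbalance exaggerates the effect to 0.48 to 0.56. Equal rates of 0.1 dilute 0.70 to 0.75 to 0.80. These ranges show that the bias can run in either direction; they do not estimate its size in this registry.

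The comparison of PPF groups is affected only indirectly, in so far as prescribing differs between diagnoses. The separately planned analyses of mortality and functional measures are unaffected.

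**What to change.** For comparisons of treatment strategies, define the primary composite from the FVC, DLCO with oxygen, 6-minute walk, respiratory hospitalisation and death components only, and count these events through any treatment change. Report treatment change separately, as the statistical section already plans, and keep the full composite as a descriptive sensitivity analysis. State which composite is used for the PPF-group comparison.

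An alternative is to count a treatment change only when documented worsening is the reason. Reasons for discontinuation are already listed in Table 1, but reasons for starting a therapy would have to be recorded as well.

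The main change needs no new data: under Visit schedule and assessments, patients may remain in the registry whatever happens to their therapy, and switches and discontinuation reasons are already secondary endpoints. It requires a wording change to the endpoint, which can be fixed in the SAP before database lock. The cost is fewer primary events and somewhat wider intervals.

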## Ethical aspects and data protection

### Ethical approval

The registry is conducted consistent with consensus ethics principles derived from international ethics guidelines including the Declaration of Helsinki, and applicable local regulatory requirements and laws.

Prior to any data collection under this protocol, written informed consent with the approved ICF is obtained from the patient or patient’s legally authorized representative, as applicable, in accordance with local practice and regulations.

Detailed information about the registry and that registry participation is voluntary will be explained to the patient. This information may be provided in a personal talk, and alternatively via telephone or videoconference. The patient will be given sufficient time to consider whether to participate in the registry. The signed ICF will be retained with the registry records. A copy of the ICF, signed and dated by the patient, must be given to the patient.

The patient can revoke registry participation at any time. As long as a patient does not recant the use of personal data, these data will be included in the intended analyses if applicable, even if the patient has resigned from the registry. Patients who have revoked their participation will not be replaced.

### Confidentiality and data protection

The sponsor as well as all investigators ensure adherence to applicable data privacy protection regulation. Data are transferred in encoded form only. The entire documentation made available to the sponsor does not contain any data which, on its own account or in conjunction with other freely available data, can be used to re-identify natural persons. The investigators are obligated to ensure that no documents contain such data.

All records identifying the subject will be kept confidential and will not be made publicly available. Patient names will not be supplied to the sponsor. If the patient’s name appears on any document, it must be obliterated before a copy of the document is supplied to the sponsor. Registry findings stored on a computer will be stored in accordance with local data protection laws.

The investigator will maintain a list to enable patients’ records to be identified in case of queries. In case of a report of a serious adverse drug reaction (SADR), the responsible pharmacovigilance person may ask for additional clarification. In that case, the company is not allowed to directly contact the patient. All additional information will be provided by the investigator.

Data protection rules will be closely followed and the standards of the General Data Protection Regulation (GDPR) will be met. Neither initials nor the exact birth date of the patient will be recorded in the database. Patient data are collected under a pseudonym. Upon saving of the first assessment (= inclusion visit), the EDC system automatically assigns a unique and consecutive Subject Identification Code (SIC). All registry documents (e.g., print outs of electronic case report forms, the informed consent forms etc. are identified with the SIC. The SIC alone cannot be used for identification of a given patient outside a site, in compliance with laws governing data privacy.

## Observational plan

### Design

This ILD registry allows for structured, non-interventional collection of data. Participating physicians will not be subject to any instructions with regard to the diagnosis and therapy of their patients. All examinations performed depend on the discretion and clinical routine of the physician.

The registry contains a basic set of variables (mandatory data) which are essential for all included patients. Another set of variables (facultative data) can be requested from the participating sites but is left to their discretion. The platform is capable for substudies (i.e., addition of further variables) in selected centres to facilitate research collaboration between institutions.

### Sites

This registry will be maintained in approximately 30 sites (hospitals and office-based) with expertise in ILD.

The number of patients per site is not limited. The study will likely be representative for expert centres in Germany.

### Patients

Patients are eligible for documentation, if they meet all of the following criteria:Fibrotic ILD*, which include all ILD groups including those with IIPs, CTD-ILD, cHP, asbestosis, sarcoidosis, etc.Age ≥ 18 yearsInterstitial lung disease on HRCT > 10% of lung parenchymaOn active anti-inflammatory, immunomodulatory, and or anti-fibrotic therapyDLco ≤ 80% predictedWritten informed consent

*Criteria of progression are not mandatory at the time of inclusion.

Patients are not eligible for documentation, if they meet one or both of the following criteria:Diagnosis of IPFParticipation in a controlled trial investigating ILD, if blinded or with investigational drug

